## Abstract

Worldwide, there is a wide gap between what women can contribute to the economy and what they actually contribute. One of the main barriers to women’s engagement in the labor market and productivity at work is the societal expectation that they should take care of their children in addition to meeting the demands of employment. Furthermore, those in informal employment face difficulties due to long working hours and environments that are not appropriate for childcare. To address this, Kidogo runs an innovative “Hub & Spoke” model for low-income communities. Here, we present a study protocol aimed at evaluating whether the provision of quality childcare opportunities for working women through the Kidogo model is feasible and acceptable and whether it contributes to improvements in their incomes and productivity at work. The study reported in this protocol which is currently ongoing, employed a quasi-experimental design with two study arms: primary caregivers who use childcare services were recruited into the intervention (*n* = 170) and comparison groups (*n* = 170). Both groups are being followed up for one year. We are using a mixed-methods approach. Appropriate statistical methods including a difference-in-differences (DID) estimator will be used to analyze the effects of the intervention. We expect that the intervention will improve the quality of childcare services which in turn will improve the incomes of the center providers. We expect that providing improved childcare services will enhance women’s economic empowerment.

**Trial registration:** PACTR202107762759962.

## Introduction

The overall purpose of the proposed project is to evaluate the effectiveness of the Kidogo model which aims at empowering women economically through the provision of quality childcare services. This goal is based on the evidence that women spend disproportionately more time on unpaid work such as childcare and household chores than men (International Labor Organization, 2008). Studies from North America, Europe, and Latin America indicate that women’s childcare responsibilities significantly impede their participation in the paid labor force. Similar barriers have been observed in sub-Saharan Africa (Doughman et al., 2017). Interventions that directly provide alternative childcare options and give women greater freedom of choice and action enable them to meaningfully contribute to economic production processes. For instance, a recent study illustrated that provision of subsidized childcare services resulted in women being more likely to engage in economic activities than those who did not have access to such services (Doughman et al., 2017). The quality and cost of paid childcare services also influence the decision to take their children to childcare and engage in employment, or stay at home and look after their children (Clark et al., 2018).

The challenges faced by women in balancing childcare and paid work are compounded in low-income urban contexts where employment opportunities are limited, and fragmented social networks often mean that mothers cannot rely on kin to provide childcare support. Further, women in informal employment face challenges such as long working hours and environments that are not conducive to carrying their babies to work or breastfeeding (Kimani-Murage et al., 2015). In awareness of this gap and to have a sustainable solution, Kidogo, a social enterprise established in 2014 (www.kidogo.co), seeks to improve access to high-quality, affordable early childhood care and education to support the healthy growth and development of young children living in urban informal settlements.

Kidogo runs an innovative “Hub & Spoke” model for low-income communities through a two-fold approach. First, by establishing best practice early childhood development (ECD) “hubs” with a holistic curriculum, the program nurtures the healthy growth and development of children, with caregivers trained on the principles of ECD. Secondly, Kidogo works to improve the quality of local childcare centers, referred to as “spokes” through its micro-franchising program with “mamapreneurs.” Mamapreneurs are local women running informal childcare centers within the community who are given a ‘business-in-a-box,’ including relevant training materials, resources, and support. In this way, Kidogo builds the capacity of facility owners to enhance self-employment opportunities.

The Kidogo hubs operate as model centers of excellence for the spokes, and act as mini-research and development (R & D) labs to test innovations and demonstration sites for the community. The hubs serve 50–100 children aged between six months and three years for eight to ten hours during the working day. Kidogo provides the basic building blocks for young children to thrive, known as “The Kidogo Way,” which includes safe, stimulating environments, trained ECD caregivers, and its proprietary play-based curriculum and health, nutrition and protection program. On weekends and during holiday months, Kidogo hubs turn into training centers for the mamapreneurs. Since 2014, Kidogo has grown to support over 130 such childcare centers serving 2886 children daily in 12 different informal settlements across Nairobi.

Addressing the burden of childcare for mothers in informal settlements enhances their opportunities to participate in gainful employment, which, in turn, may contribute to improved nurturing care for their children. By improving the quality, consistency, and availability of childcare and pre-school services in communities, Kidogo is able to give young children the best start to life, while providing working mothers peace of mind that allows them to find and maintain gainful employment, and ultimately transform the overall trajectory of the family.

Kidogo’s impact to date has however only been measured in terms of improvements in children’s outcomes, the number of mamapreneurs who have been supported, and the number of hours undertaken in providing training and mentorship visits to mamapreneurs (https://www.kidogo.co/impact). There has been no research study measuring the effect of the Kidogo model on women’s economic empowerment at both the caregiver and mamapreneur levels. The proposed research effort, therefore, seeks to evaluate how the Kidogo model can be scaled to enhance the economic outcomes of women living in low-income communities in Kenya. Specifically, the project will: (a) determine the effectiveness of the Kidogo model on women’s (caregivers and mamapreneurs) labor outcomes such as labor force participation, economic productivity, and economic empowerment; (b) identify what works within the Kidogo model, which aspects could be scaled up and what modifications are required; and (c) establish the cost and cost-effectiveness of the Kidogo model to guide policy discussions on the provision of affordable childcare.

### Theoretical framework and theory of change

We conceptualize women’s economic empowerment based on a theoretical framework developed by (Kabeer 1999). Kabeer posits that empowerment is the expansion of people’s ability to make strategic life choices in a context where this ability was previously denied to them. The ability to exercise choice is thought of in terms of three interrelated dimensions: resources, agency, and achievement. Resources include material, human and social resources. Agency refers to people’s capacity to define their life choices and to pursue their own goals. Taken together, resources and agency constitute “capabilities: the potential that people have for living the lives they want, of achieving valued ways of ‘being and doing’ or ‘functioning achievements.’”

The theory of change is based on our experience that the provision of quality childcare services results in women being able to make informed choices about their labor participation. We expect that in the short term, the intervention will improve access to quality childcare services and avail women’s time to enable them to participate in the productive sphere, as they will spend less time in the reproductive sphere (e. g., engaging in child-rearing activities). The childcare centers will provide an opportunity for women to meaningfully engage in economic activities for, at the very least, the required number of working hours in a day. This is essential for them to optimize their income and improve their economic productivity and bargaining power within the household beyond the intervention period. Ultimately, this will contribute to reducing the gender gap in labor participation. In the long term, we anticipate that women will be economically empowered, and the findings will contribute to changes in policy and practice. In creating this change, the program proposes a menu of multifaceted but targeted interventions at three levels: individual, childcare facility, and community (Fig. 1).

**Fig. 1 Fig1:**
[figure not shown]
Theory of change illustrating pathways to women's economic empowerment.

The project will adopt a holistic perspective that considers that sustained impacts can only be achieved through significant engagement with caregivers, center care providers, and communities. At the caregiver level, primary caregivers will receive training on how to engage in appropriate ECD practices. At the center care provider level, mamapreneurs will receive training on how to enhance quality within the childcare centers. The training will be delivered to groups of parents and mamapreneurs separately. Mamapreneurs within the community will also receive continued support for running and expanding their micro-enterprises. The broader community will be continually involved as stakeholders through monthly engagements and regular communications about the Kidogo Program activities.

### Gender considerations in childcare

Gender inequality and related discriminatory practices are global problems. Even in nations perceived to have attained basic gender equality, for example, the Nordic countries (Zahidi, 2013) the bone of contention has always been that intangible aspects of discrimination against women have not yet been fully eradicated. For instance, men are more likely than women to be in managerial positions. Moreover, women are more likely to engage in unskilled, low-wage labor, or spend less time in income-generating work and more time in unpaid caregiving work than men. Unpaid care work, which encompasses direct care of persons, housework and unpaid community work includes minding children while also engaging in routine household activities, managing children’s schedules, and taking care of children when they are unwell (Samman et al., 2016). Across the world, women working full-time earn 85% of the wages that men earn for the same work and level of education, thus limiting their ability to access and maintain their families’ needs, including providing children with quality care and education (United Nations Population Fund, 2017). It is against this backdrop that significant efforts are needed to level the playing field insofar as the economic empowerment of women is concerned (Gertler et al., 2012; Payne & Nicholls, 2010).

Apart from the gender discrimination that women experience at the workplace, they are increasingly separated from their children in the first year for a significant amount of time because of employment. Reports show that over half of women with a child less than one year are in employment (Baxter, 2008; Heymann & Kramer, 2009; Payne & Nicholls, 2010) and many may be unable to breastfeed their children for most of the day due to a lack of appropriate space and facilities at the workplace. Low-income laborers are more vulnerable than professional women as the former are less likely to have a private office to express milk or a work environment that is supportive of childcare issues (Amin et al., 2011; Brasileiro et al., 2010; Chen et al., 2013; Ortiz et al., 2004). As such, supporting their childcare needs presents a tremendous opportunity in addressing any issues they may have in childcare provision.

Findings from studies conducted in Mukuru kwa Njenga and Korogocho (Muendo, 2014) show a strong relationship between the provision of childcare services and women’s engagement in work, particularly for low-income employment activities. These studies demonstrated that some of the benefits associated with the provision of childcare services include increased earnings, improved mobility, and an increase in the number of hours worked. In both developing and developed countries, childcare centers have demonstrated up to six-fold increases in breastfeeding and exclusive breastfeeding rates in the first six months, with a stronger impact in developing countries (Imdad et al., 2011). Other benefits associated with the establishment of workplace childcare centers include better employee performance, lower absenteeism rates among employees (Gullekson et al., 2014), and greater peace of mind for mothers. Ultimately, these interventions have shown improvements in women’s participation in the labor force, enhanced improved preparedness for school among their children, and led to increased productivity which consequently results in the country’s economic growth. At the same time, the safety and optimal growth of young children are attained.

## Methods

### Study design

The study reported in this protocol will employ a quasi-experimental design with two study arms, that is, intervention and comparison groups. We will use a mixed-methods approach that combines quantitative, and qualitative data collection methods and records review. We will engage the members of the sub-county and county Health, Education and Social Services Departments to guide decisions on the selection of specific sites for the study implementation. The study sites will be randomly assigned to the intervention and comparison arms with a buffer zone between them to minimize contamination. The participants in the childcare centers within each study site will be purposively selected, and the study arms will be matched based on population size and background characteristics. The intervention arm will comprise women using childcare services provided through the Kidogo hub and spokes while the comparison arm will comprise women using childcare services from other centers that are not supported by Kidogo.

### Study site

The study will be conducted in Nakuru Town West sub-County in Nakuru County. There are five wards in Nakuru Town West sub-County, namely Kaptembwa, London, Rhonda, Shaabab, and Baruti. Kidogo has had substantial coverage and significant influence in Nairobi. For us to evaluate the impact of the Kidogo model effectively, we need to use a “virgin” setting where such an intervention has not been conducted before and therefore, we will utilize the opportunity of Kidogo’s plans to extend their model to other communities including Nakuru. Nakuru is the fourth largest city in Kenya and has been selected because a large proportion of the inhabitants (206,695) live in informal settlements (Kenya National Bureau of Statistics, 2019) with a higher proportion reported in Nakuru Town West sub-County. Similar to Nairobi slums, informal settlements in Nakuru are characterized by high levels of poverty, with the majority of residents engaging in low-paid jobs. Women face challenges with access to quality childcare and have to juggle between family responsibilities (childcare) and engaging in paid work to earn an income to support their families. The community, therefore, stands to benefit from the Kidogo intervention.

### Description of the intervention

Kidogo will establish one to two model centers of excellence for quality childcare with 45–60 children in each. One will be a community hub, while the other will be supported by a private employer. Kidogo will also support 20–40 spokes linked to these hubs, with between 10 and 15 children in each. Spokes will be identified by mapping all childcare centers and recruiting those that will be eligible and willing to participate. Through the social franchising approach, Kidogo will provide training, mentorship, and materials (Starter Kit—a set of materials and resources provided by Kidogo) to the mamapreneurs to help them improve the quality, profitability and expansion of their childcare micro-businesses. Specifically, Kidogo will take mamapreneurs through a 9-month program that offers monthly workshops on an ECD or business-related theme. This will be followed by a bi-weekly, two-hour on-site coaching/mentoring visit by a Franchising Officer.

In recognition of the limitations of in-person interactions occasioned by the COVID-19 pandemic, Kidogo will include a smartphone in its Starter Kit to enable the mamapreneurs to participate virtually in training, receive updates, and have meetings with the franchising team. The internet costs will be borne by Kidogo. The phones will also enable the team to follow up on the business operations of the mamapreneurs in real-time. Primary caregivers in the intervention arm will receive monthly parenting messages.

### Study participants

The primary beneficiaries of this project are mothers with young children below the age of three years. Our sampling frame will include all the women and children who use the childcare services in the hub and spokes, alongside those who use the centers that are not supported by Kidogo. Using the list of childcare centers generated through the mapping activity by the Kidogo team, we will purposively select childcare centers and childcare center caregivers for inclusion in the intervention and control arms. Subsequently we will purposively select primary caregivers receiving childcare services in the sampled childcare centers to be recruited into the intervention and control arms. All the mamapreneurs (intervention arm) and childcare center caregivers (control arm) in the selected childcare centers will be included as secondary beneficiaries.

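### Random assignment of sites does not protect against selection of centres and women, and the planned matching and difference-in-differences may not fully remove it

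*Protocol article*

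**What the plan says.** The protocol article describes selection at three levels.

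- **Sites** (Study design): "The study sites will be randomly assigned to the intervention and comparison arms with a buffer zone between them to minimize contamination".
- **Centres.** Description of the intervention: "Spokes will be identified by mapping all childcare centers and recruiting those that will be eligible and willing to participate". Study participants, working from a centre list produced by the implementer's mapping: "we will purposively select childcare centers and childcare center caregivers for inclusion in the intervention and control arms".
- **Women.** Study design: "The participants in the childcare centers within each study site will be purposively selected". Study participants: "we will purposively select primary caregivers receiving childcare services in the sampled childcare centers".

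Three devices are offered for comparability. Study design says that "the study arms will be matched based on population size and background characteristics". Data analysis adds propensity score matching of participants on their observable characteristics, and a DID estimator, which it credits with removing the baseline difference in the outcome. Data analysis also promises a test of parallel pre-intervention trends. Data management schedules one baseline on joining, then surveys at 6 and 12 months.

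The article calls the design quasi-experimental. The Abstract reports recruitment in the past tense and follow-up as under way.

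**The concern.** Randomising sites makes the centres and women in the two arms comparable in expectation only if those who enter the study are taken by the same rule in each arm, or at random. Here the stated rule for intervention spokes includes willingness to join the programme, and both centres and women are then picked by judgement. Providers who volunteer for training, coaching and business support may differ from other providers, and their clients may differ too. If such differences affect how women's work outcomes change over the year, the DID estimate mixes them with the effect of the programme. The effectiveness and cost-effectiveness conclusions, which the article intends for policy and scale-up, would carry that mixture.

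**Working it through.** The plan gives no figure for this point, so the check is mainly a reading of the sections against each other. Two illustrations for scale follow.

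**1. What is random.** Only the site. Entry of spokes depends on eligibility and willingness; inclusion of centres and women is purposive in both arms.

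**2. What each safeguard covers.**

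| Safeguard (section) | Covers | Leaves open |
|---|---|---|
| Arm matching (Study design) | Population size, background characteristics | Centre willingness or quality, not named |
| Propensity matching (Data analysis) | Participants' observable characteristics | Unobserved traits; centre-level traits unless included |
| DID (Data analysis) | Outcome differences constant over time | Different trends |
| Parallel-trends test (Data analysis) | Would probe different trends | Needs at least two pre-intervention waves; one is scheduled |

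The last row matters most. A pre-intervention trend is a change between two earlier time points. The 6- and 12-month surveys both fall after the start, so the study's scheduled data cannot supply one.

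**3. Room for discretion** (Description of the intervention). Fewest child places: 20 × 10 + 1 × 45 = 245. Most: 40 × 15 + 2 × 60 = 720. The 170 intervention women would be 170/245 = 69% to 170/720 = 24% of places, treating one place as one woman and before refusals. Choice among women is limited at the low end and wide at the high end.

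**4. Illustration of DID bias** (assumed values, not trial data). Let the true effect be zero, the women be identical between arms, centre motivation be standard normal, intervention centres come from the more motivated half, and comparison centres be unselected. Mean motivation in the upper half is √(2/π) = 0.80 SD. If motivation shifts the 12-month change by g SD per SD, the expected bias is 0.80 × g:

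- g = 0 (motivation affects level only): 0.00 SD
- g = 0.1: 0.08 SD
- g = 0.2: 0.16 SD
- g = 0.3: 0.24 SD

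Simulation gave the same values to within rounding (0.00, 0.08, 0.16, 0.24), and about zero when centres were unselected in both arms.

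**5. Illustration of the false-positive rate.** Inputs from Sample size calculation: 170 per arm, 10% attrition, design effect 1.5, absence 4/24 and 2/24. Absence is treated as a proportion of women, as in that section's formula.

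- Effective n per arm = 170 × 0.9 / 1.5 = 102
- p = (4/24 + 2/24)/2 = 0.125
- SE of one difference = √(2 × 0.125 × 0.875 / 102) = 0.0463
- SE of DID = 0.0463 × √(2(1 − r)), which is 0.0655 at r = 0 and 0.0463 at r = 0.5. The baseline–endline correlation r is assumed.
- Rate = Φ(−1.96 + b/SE) + Φ(−1.96 − b/SE), where b is the differential trend

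| b | r = 0 | r = 0.5 |
|---|---|---|
| 1 point | 5.3% | 5.5% |
| 3 points | 7.4% | 9.9% |
| 5 points | 11.9% | 19.1% |

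Nothing in the document says which b, if any, applies.

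**The case against.** The selection is not hidden. The design is labelled quasi-experimental, and the sentence on purposive selection goes on to state arm matching; purposive choice may be the means of achieving that match. The willingness condition stands in a section about the intervention, where comparison-centre criteria would not be expected, and a condensed article may leave those criteria to the full protocol. The variables for propensity matching are not listed, so centre variables are not expressly excluded. Volunteering is part of a franchise model, and the effect among willing centres may be the effect of interest.

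Much of this stands, and it rules out some stronger readings:

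- A reader might infer that comparison centres faced no screen. The article is silent on this and does not say so.
- A reader might infer that all selection was made with the arm known. The frame of women is defined by whether their centre has the implementer's support, but the order of mapping, site assignment and centre selection is not given.
- A reader might infer that the implementer's list is itself biased. The mapping is described as covering every childcare centre.

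What the objection does not answer is the rule that is stated. Purposive selection of centres and women in both arms is in the text. Even if the effect among willing centres is the target, the comparison still needs centres that would have been willing. Disclosing the design does not make the trend assumption testable.

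**Conclusion.** The point holds in a limited form. Random assignment at site level does not secure comparability of the centres and women actually studied, and the planned matching and DID may not fully restore it. DID does remove fixed level differences; the exposure is to differences in trend, which one baseline wave cannot check.

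It would be tempting to conclude that bias is built in and favours the intervention. The document does not support that. Volunteering centres could be the thriving ones or the struggling ones, and no section links a provider's motivation to a trend in her clients' absence from work. The size and direction of any residual bias cannot be determined. The figures of 0 to 0.24 SD and 5.3% to 19% show only what assumed trends would do.

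This should be addressed: the effect estimate rests on an assumption that the selection procedure puts at risk and the planned check cannot assess.

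**What to change.** **Where selection is still open:** apply the same eligibility-and-willingness screen to centres in both arms, for example by asking comparison centres whether they would join if offered. Replace purposive selection of women with all eligible users, or a random draw from each selected centre's users. This requires a user list per centre; the article describes a compiled list of centres only.

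**Where recruitment has closed, as the Abstract suggests:**

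1. Add a few centre-level baseline variables, such as enrolment, fee, staffing and years open, to the propensity model. Willingness itself cannot serve as a covariate, since every recruited spoke has it.
2. Drop the parallel-trends test, or state that it is not possible with one pre-intervention wave and that parallel trends are assumed.
3. Interpret and report the effect as a non-randomised comparison, despite the random assignment of sites.

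**Cost:** modest collection of centre-level data, changes of wording, and a more cautious conclusion.
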